| | Discuss the research design including but not limited to such issues as: probability of group assignment, potential for subject to be randomized to placebo group, use of control subjects, etc. | | --- | | |  | Twenty participants will complete procedures during treatment with placebo and study medication, in random order, using a within-subjects, double-blind, placebo-controlled design. There will be a two week period between each phase. The dose of doxazosin needed to alter the effects of cocaine is unknown and preclinical animal studies have not been conducted. Because of this, initially we will study the effects of a low dose of doxazosin (4mg daily) compared to placebo daily. Because this class of medication needs to be titrated upward due to the potential for hypotension, treatment will begin at 1mg and increased by 1mg increments every three days until 4mg is reached. Placebo will be dosed identically. Blood pressure (resting and orthostatic) will be assessed daily prior to dosing. Cocaine (0, 20, and 40mg) will be administered during treatment with 4mg doxazosin/placebo. On day 10, cocaine will be administered in ascending dose (20mg followed by 40mg) with the 0mg dose randomly interspersed to maintain the blind. Cardiovascular measures and subjective effects ratings will be assessed following cocaine administration. Participants will be monitored for stability on days 11 and 12 and discharged from the hospital on day 13. Discharge will only occur for subjects who have a supine BP of 100/65 mm Hg or higher, a seated blood pressure of 90/60 mm Hg or higher, and an orthostatic change upon standing of < 20 mm Hg systolic or < 10 mm Hg diastolic.  If 4mg doxazosin treatment is well tolerated but is not associated with alterations in the effects of cocaine, a second group of subjects will be studied using the same sample size. Treatment will begin at 1mg and increased by 1mg increments every three days until 8mg is reached. All study procedures will be identical as described above. Placebo will be dosed identically. | | --- | --- | | |

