| | Inclusion Criteria: | | --- | | |  | 1. Be English-speaking volunteers who are not seeking treatment at the time of the study; 2. Be between 18-55 years of age; 3. Meet DSM-IV TR criteria for cocaine dependence; participants may or may not meet criteria for nicotine dependence. Nicotine dependence is allowed but not required because most cocaine users smoke cigarettes. 4. Have a self-reported history of using cocaine by the smoked or IV route; 5. Have vital signs as follows: supine blood pressure > 100/65 mm Hg, a seated blood pressure of > 90/60 mm Hg and < 150/90 mm Hg, and an orthostatic change < 20 mm Hg systolic or <10 mm Hg diastolic on standing. Resting pulse must be < 90 bpm. 6. Have hematology and chemistry laboratory tests that are within normal (+/- 10%) limits with the following exceptions: a) liver function tests (total bilirubin, ALT, AST, and alkaline phosphatase) < 3 x the upper limit of normal, and b) kidney function tests (creatinine and BUN) within normal limits; 7. Have a baseline EKG that demonstrates clinically normal sinus rhythm, clinically normal conduction, and no clinically significant arrhythmias; 8. Have a medical history and brief physical examination demonstrating no clinically significant contraindications for study participation, in the judgment of the admitting physician and the principal investigator. | | --- | --- | | |

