| | Exclusion Criteria: | | --- | | |  | 1. Meet DSM IV TR criteria for dependence on drugs other than cocaine or nicotine. 2. Have any history or evidence suggestive of seizure disorder or brain injury; 3. Have any previous medically adverse reaction to cocaine, including loss of consciousness, chest pain, or epileptic seizure; 4. Have neurological or psychiatric disorders, such as: • psychosis, bipolar illness or major depression as assessed by MINI; • organic brain disease or dementia assessed by clinical interview; • history of any psychiatric disorder which would require ongoing treatment or which would make study compliance difficult; • history of suicide attempts within the past year and/or current suicidal ideation/plan; 5. Have evidence of clinically significant heart disease or hypertension, as determined by the PI; 6. Have evidence of untreated or unstable medical illness including: neuroendocrine, autoimmune, renal, hepatic, or active infectious disease; 7. Have symptomatic HIV or are taking antiretroviral medication; 8. Be pregnant or nursing. Other females must either be unable to conceive (i.e., surgically sterilized, sterile, or post-menopausal) or be using a reliable form of contraception (e.g., abstinence, birth control pills, intrauterine device, condoms, or spermicide). All females must provide negative pregnancy urine tests before study entry, upon hospital admission, and at the end of study participation; 9. Have asthma or currently use theophylline or other sympathomimetics; 10. Have any other illness, condition, or use of psychotropic medications, which in the opinion of the PI and/or the admitting physician would preclude safe and/or successful completion of the study.  Criteria for Discontinuation Following Initiation Participants will be discharged if they have a positive breath test indicating use of alcohol or a urine test indicating illicit use of drugs while in the MED-VAMC, if they do not comply with study procedures, or if they do not tolerate the study drugs. Stopping criteria are detailed below.  Stopping Criteria Cocaine administration will not be initiated if there are clinically significant arrhythmias or if vital signs are outside of acceptable ranges, which are resting pulse < 130 bpm and blood pressure below 165mm Hg systolic and 100mm Hg diastolic. In addition, repeated doses of cocaine will not be administered (and the study physician will halt continued cocaine delivery) if there are behavioral manifestations of cocaine toxicity (agitation, psychosis, inability to cooperate with study procedures).   Stopping Criteria for Further Participation Subject participation will be terminated if any of the following events occur: 1. Systolic BP greater than 180 mm Hg sustained for 5 minutes or more; 2. Diastolic BP greater than 120 mm Hg sustained for 5 minutes or more; 3. Heart rate greater than (220 – age x 0.85) bpm sustained for 5 minutes or more. Note: if a single value exceeding the values above is detected, the readings will be repeated until it is determined whether or not the stopping criteria have been met.  Subject Selection Criteria Rationale Route of administration. Participants are required to have used cocaine by the IV or smoked route to avoid exposing participants to drugs by routes of administration that produce more intensive interoceptive effects than usually used by the participants. Prior experience with smoked cocaine is allowed (rather than restricting the population to those with experience with IV cocaine) because smoked cocaine reaches brain sites of action as rapidly as does intravenously administered cocaine and smoked cocaine produces effects that are comparable to IV cocaine. Speed of administration (and rate of delivery to brain) of stimulant drugs likely impacts subjective and cardiovascular effects, so smoked and intravenously administered cocaine produce similar subjective effects (22-26). | | --- | --- | | |

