| F2.  Procedure |
| |  | | --- | | |  | Screening Interested candidates will receive an explanation of the study purpose and requirements. If still interested, the candidates will be allowed to review, inquire about, and sign the study informed consent form. After providing informed consent, subjects proceed to the screening assessment phase of the study. A urine drug toxicology screen will be conducted for drugs of abuse. Some of this sample will be shared with Rice university to develop new tests for drug detection. A saliva sample will also be collected for this purpose. Candidates deemed eligible based on initial screening assessments will be administered a MINI by a trained mental health professional, to determine if there are any psychiatric conditions that might exclude the potential subject from participation. Blood will be collected for analysis of hematology and chemistry tests. These assessments must be completed within 14 days before intake. At the initial screening visit, restrictions on use of alcohol, drugs of abuse, and medications will be reviewed. All subjects will be required to sign a written statement that they will abstain from use of cocaine or other psychostimulants throughout the duration of their participation in the trial.  All applicants for study participation will receive counseling as part of their participation, and will be advised that treatment for drug abuse is indicated and available. Applicants not participating in the study will receive treatment referral information as appropriate. At completion of their participation, study subjects will again be advised that treatment is indicated and available, and will be given treatment referral information and assistance.  Participants will reside on the Research Commons for the duration of the study (about 28 days total). Participants must refrain from illicit and prescription drug use, and we will confirm compliance by urine testing and breath alcohol level testing. Passes and monitoring. Passes will not usually be allowed, and visitors will not be permitted. Participants’ belongings will be searched upon arrival.  The study schedule outlined below may change by a day or two due to scheduling issues and/or safety reasons. We will ask participants to complete the protocol twice (once being randomized to placebo and once being randomized to doxazosin, but this wont be required.   General Procedures: Participants will be studied while residing on the Research Commons. Cocaine administration sessions will be conducted at approximately the same time of day for a given participant. Experimental sessions will be several hours in duration and will be conducted in a quiet room with research and medical staff present. The room will contain an experimental station, equipped with a response console attached to a personal computer and video monitor. Heart rate, EKG, and blood pressure will be recorded throughout experimental sessions using an automatic monitoring system.   Smoking, caffeine, and food. Caffeine and food will be prohibited during and 90 min before study sessions excepting a 1 hour break for lunch.   Day 1-10: The study participants will be randomized to receive either doxazosin or placebo. Doxazosin treatment will begin at 1mg and will be increased by 1mg increments every three days until 4mg is reached. Placebo will be dosed identically. Prior to dosing doxazosin, and at 1 hour intervals after each dose from hours 2 through 6 after dosing, sitting and supine orthostatic blood pressure will be assessed.  Cardiovascular monitoring and discontinuation criteria For doxazosin to be administered, the following criteria must be met: 1. supine blood pressure above 100/65 mm Hg, 2. a seated blood pressure of above 90/60 mm Hg, 3. and an orthostatic change smaller than 20 mm Hg systolic or smaller than 10 mm Hg diastolic on standing. The dose will not be increased until the participant has met criteria for dosing and has received 3 doses at a given dose level.  a. Participants who do not meet the criteria above at any time during hours 2 through 6 after dosing will remain supine until the next BP assessment. b. Participants who do not meet the criteria above consistently from hours 2 through 6 after any dosing will not have their dose of doxazosin increased and will remain at the prior dosing level. c. Participants who do not meet the requirements for dosing increase (supine blood pressure > 100/65 mm Hg, a seated blood pressure of > 90/60 mm Hg, and an orthostatic change < 20 mm Hg systolic or <10 mm Hg diastolic on standing) for 6 days will have medication discontinued and they will be discontinued from the study.   Day 10: Cocaine 20mg, 40mg and matched placebo saline will be administered via IV push by the study physician on day 10, at hourly intervals, with the placebo dose randomly interspersed to maintain the blind. To ensure that subjects will not be at risk from cocaine, the resting pulse must be < 90 bpm and the blood pressure must be < 150 mmHg systolic and < 90 mmHg diastolic immediately prior to dosing. Heart rate and blood pressure measurements will be made prior to cocaine dosing and at 15-minute intervals thereafter until 30 minutes following the final dose. Visual-analogue scale ratings of “any cocaine effect”, “high”, “good effects”, “bad effects”, “like cocaine”, “desire cocaine”, “depressed”, “anxious”, “stimulated”, and “if you had access to cocaine right now, how likely would you be to use it?” will be collected at -15 min, 5 min, 10 min, 15 min, 20 min, 30 min, and 45 min after cocaine dosing. Participants will remain seated during experimental sessions except for brief visits to the lavatory.   All infusions will be administered in single-blind fashion. All experimental procedures will be conducted in a hospital room located in the GCRC. Infusions will be administered over 2 minutes by I.V. push. Vital signs must remain within values specified under Stopping Criteria for initiation of cocaine administration. An ACLS-certified physician will be present from 15 min before drug administration until at least 1 hour after cocaine administration. The physician will be available in house and on pager for at least 4 hours after drug administration. Heart rate will be measured using continuous ECG from 15 min prior to cocaine or placebo dosing until 2 hours after dosing. Blood pressure will be assessed at frequent intervals from 15 min prior to cocaine or placebo dosing until 2 hours after dosing.   Discharge Participants will be monitored for stability on days 11 and 12 and discharged from the hospital on day 13. Discharge will only occur for subjects who have a supine BP of 100/65 mm Hg or higher, a seated blood pressure of 90/60 mm Hg or higher, and an orthostatic change upon standing of < 20 mm Hg systolic or < 10 mm Hg diastolic. Prior to discharge subjects will have a physical examination and vital signs, and complete the Beck Depression Inventory-II. An assessment of adverse events will be completed.  Participants will have the choice of returning two weeks later to complete study procedures.   Stopping Rules Doxazosin Participants who do not meet the criteria listed above (supine blood pressure above 100/65 mm Hg, a seated blood pressure of greater than 90/60 mm Hg, and an orthostatic change smaller than 20 mm Hg systolic or smaller than 10 mm Hg diastolic on standing) at any time during hours 2 through 6 after dosing will remain supine until the next BP assessment. Participants who do not meet the criteria above consistently from hours 2 through 6 after any dosing will not have their dose of doxazosin increased and will remain at the prior dosing level. Participants showing syncope or dizziness that does not respond to sitting down will be discharged from the study.  Stopping Criteria for Further Participation Participants who do not meet the requirements for dosing increase for 6 days will have medication discontinued and they will be discontinued from the study.  Cocaine Cocaine will not be administered if there are clinically significant arrhythmias or if vital signs are outside of acceptable ranges, which are resting pulse below 90 bpm and blood pressure below 150mm Hg systolic and 90mm Hg diastolic. In addition, repeated doses of cocaine will not be administered (and the study physician will halt continued cocaine delivery) if there are behavioral manifestations of cocaine toxicity (agitation, psychosis, inability to cooperate with study procedures).   Stopping Criteria for Further Participation Subject participation will be terminated if any of the following events occur: 1. Systolic BP above 180 mm Hg sustained for 5 minutes or more; 2. Diastolic BP above 120 mm Hg sustained for 5 minutes or more; 3. Heart rate above (220 – age x 0.85) bpm sustained for 5 minutes or more. Note: if a single value exceeding the values above is detected, the readings will be repeated until it is determined whether or not the stopping criteria have been met.  Adverse event assessment and management. We will assess participants’ well-being daily. Spontaneously reported symptoms or complaints will be recorded and reported to the IRB and NIDA and the FDA if events are classified as serious. Specific guidelines have been developed to guide assessment and intervention in the event of cardiovascular toxicity, such as malignant hypertension, ventricular arrhythmia, chest pain, etc., and are in use for our other studies involving cocaine administration. These guidelines are intended to support rather than supersede clinical judgment. If needed, a code team responds. Participants needing to be transferred to a medical or ICU ward can be, though this has never been necessary.   Assessments see attached | | --- | --- | | |

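### The heart-rate limit that ends participation is printed as 220 − 0.85 × age, above 220 − age at every eligible age, and the orthostatic limit uses *or* where it needs *and*

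*Protocol*

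**What the plan says.** **Heart rate.** Protocol section F1 (Stopping Criteria for Further Participation, placed after the exclusion criteria) introduces its list with "Subject participation will be terminated if any of the following events occur". The third event is "Heart rate greater than (220 – age x 0.85) bpm sustained for 5 minutes or more". Section F2 repeats the rule for cocaine as "Heart rate above (220 – age x 0.85) bpm sustained for 5 minutes or more". The bracket is in the same place both times, and no value in bpm is worked out anywhere. The ages to which it applies come from inclusion criterion 2: "Be between 18-55 years of age".

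**Orthostatic change.** The criterion appears six times:
- F1, Design, discharge: "an orthostatic change upon standing of < 20 mm Hg systolic or < 10 mm Hg diastolic". F2, Discharge, uses the same words.
- F1, inclusion criterion 5: "an orthostatic change < 20 mm Hg systolic or <10 mm Hg diastolic on standing". F2 uses the same words in item c, on dose increases.
- F2, third condition for giving doxazosin: "an orthostatic change smaller than 20 mm Hg systolic or smaller than 10 mm Hg diastolic on standing". F2, Stopping Rules for doxazosin, uses the same words.

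Each time it is something the participant has to satisfy, alongside a supine floor of 100/65 mm Hg and a seated floor of 90/60 mm Hg. F1 gives the reason for caution: "this class of medication needs to be titrated upward due to the potential for hypotension".

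**The concern.** Both rules are thresholds on which staff act directly, and both appear looser on paper than a safety rule should be.

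A factor of 0.85 in a heart-rate stopping rule would be expected to bring the limit below 220 − age. As printed it does the reverse. A bracket around the whole expression also serves no arithmetic purpose, which suggests that it was meant to close after *age*. This is the only heart-rate criterion by which a participant is withdrawn after cocaine.

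In the orthostatic rule, *or* inside a pass condition means that meeting one component is enough. A participant with a large systolic fall and a small diastolic fall would satisfy the criterion for entry, dosing, dose increase and discharge. Orthostatic hypotension is the hazard the titration is meant to control, and haemodynamic safety is part of the primary objective in Section D.

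**Working it through.** **Heart rate**

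Inputs: the printed formula (F1 and F2) and ages *a* from 18 to 55 (inclusion criterion 2). The plan gives no worked value to reproduce, so the formula is evaluated as written. Multiplication comes before subtraction, and the bracket encloses everything, so the limit is 220 − 0.85*a*:

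- Age 18: 220 − 15.3 = 204.7 bpm
- Age 40: 220 − 34 = 186 bpm
- Age 55: 220 − 46.75 = 173.25 bpm

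| Age | As printed, 220 − 0.85*a* | 220 − *a* | (220 − *a*) × 0.85 | Printed limit as % of 220 − *a* |
|---|---|---|---|---|
| 18 | 204.7 | 202 | 171.7 | 101.3 |
| 40 | 186 | 180 | 153 | 103.3 |
| 55 | 173.25 | 165 | 140.25 | 105.0 |

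Two identities show that the pattern holds at every age:

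- Printed limit minus (220 − *a*): (220 − 0.85*a*) − (220 − *a*) = 0.15*a*, which is always positive. It is 2.7 bpm at 18, 6 at 40 and 8.25 at 55.
- Printed limit minus the limit with the bracket moved: (220 − 0.85*a*) − (187 − 0.85*a*) = 220 − 187 = 33 bpm, whatever the age.

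For a 40-year-old, a sustained rate of 154 to 186 bpm does not meet the printed rule. With the bracket moved, any sustained rate above 153 bpm does.

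**Orthostatic change**

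Let *s* and *d* be the systolic and diastolic falls on standing. As printed, a participant passes if *s* < 20 or *d* < 10, and therefore fails only if *s* ≥ 20 and *d* ≥ 10 together.

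| Fall (mm Hg) | Passes under *or* | Passes under *and* |
|---|---|---|
| 19/9 | yes | yes |
| 10/15 | yes | no |
| 35/8 | yes | no |
| 20/10 | no | no |

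The supine and seated floors do not close the gap. As an illustration, with values chosen for this purpose: supine 120/75, seated 105/70, standing 85/67.

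- The supine floor (100/65) and the seated floor (90/60) are both met.
- Measured from supine, the fall is 120 − 85 = 35 systolic and 75 − 67 = 8 diastolic. It passes under *or* because 8 < 10, and fails under *and* because 35 ≥ 20.
- Standing systolic pressure, 85, is below the seated floor of 90. Neither floor applies to standing pressure.
- The protocol does not name the reference position. Measured from seated, the fall is 20/3, which again passes under *or* and fails under *and*.

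Elsewhere the protocol joins paired upper limits with *and*: 150 systolic and 90 diastolic before cocaine in F2, and 165 systolic and 100 diastolic in the F1 stopping criteria. The orthostatic wording departs from that usage.

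**The case against.** The arithmetic is not in dispute. The case on the other side concerns consequence and intent.

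*Other controls exist.* Participants who do not tolerate the study drugs are discharged. The pre-dose pulse limit is printed as 130 bpm in F1 and 90 bpm in F2, and a rate of 154 bars the next cocaine dose under either. Section H1 withholds further cocaine until cardiovascular values return to preset limits. There is continuous ECG, a physician in the room, cardiovascular toxicity guidelines and a code team, and separate withdrawal limits at 180 systolic and 120 diastolic. This stands as mitigation. The heart-rate error therefore bears mainly on when participation ends and whether the participant could be re-challenged in the second phase, not on whether cocaine continues at that rate. None of these controls sets the withdrawal threshold.

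*The intended formula is inferred.* This stands. The protocol neither calls 220 − age a maximum heart rate nor names 85% as a target.

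*The orthostatic *or* may be loose prose for two limits, neither to be exceeded.* Staff may well read it that way. But a written safety limit should not depend on being read against its literal sense, and *and* is harmless if the protective reading is already in use.

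*Entry and discharge also need clinical judgment* (inclusion criterion 8; the physician's evaluation before discharge in H1). This stands, so satisfying the orthostatic rule is not sufficient for either. Dosing and dose increases have no comparable written judgment, and there the wording matters most.

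**Conclusion.** Both rules are wrong as written and should be corrected.

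The literal heart-rate limit is 204.7 bpm at age 18, falling to 173.25 at age 55. It is 0.15 × age above 220 − age throughout, and this needs no assumption. The gap of 33 bpm, and limits of 171.7 to 140.25 bpm, rest on the assumption that 85% of 220 − age was intended. That is the natural reading but needs clinical confirmation.

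Read literally, the orthostatic rule fails only those who breach both limits at once. This conclusion depends on the literal reading of *or*. The 35/8 example shows what that reading permits and does not estimate how often it would occur. The other safeguards lessen the likely harm but repair neither threshold.

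**What to change.** - **Heart rate:** once the sponsor's clinicians confirm the intent, print the limit as (220 − age) × 0.85 bpm in F1 and F2. A worked value, such as 153 bpm at age 40, would prevent the slip from recurring.
- **Orthostatic change:** replace *or* with *and* in all six statements: F1 Design (discharge), inclusion criterion 5, and in F2 the dosing condition, item c on dose increases, Discharge, and the doxazosin stopping rule.

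On paper the cost is one moved bracket in two places and one word in six, with no change to design or sample size. In practice it depends on how staff now read *or*. If they read it protectively, nothing changes. If they read it literally, some dose increases will be held and some participants may not qualify. With three doses at each of 1, 2 and 3 mg, 4 mg is first reached on day 10, the cocaine day, so a held increase could leave a participant below 4 mg unless the schedule allowance of a day or two covers it. The protocol gives no basis for estimating how often that would happen. It is the ordinary cost of applying the safety limit.

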|  |
| **Section G:  Sample Size/Data Analysis** |
| G1.  Sample Size |
| | How many subjects (or specimens, or charts) will be used in this study? | | --- | | |  | Local: 200              Worldwide: 200 | | --- | --- | | |
| | Please indicate why you chose the sample size proposed: | | --- | | |  | Rationale for sample size: The power analysis is based on a published report on the subjective and physiological effects of intravenous cocaine (Foltin & Fischman, 1991). One of the commonly used items “Feel High” was chosen for power analysis. We anticipate a reduction by one-half as a clinically significant treatment effect. For a sample size of 20, with an alpha level of 0.05, a paired t-test indicates power of approximately 0.80.   To have twenty completers, we may need to enroll up to 30 participants and thus screen/consent 200 potential subjects. | | --- | --- | | |
| G2.  Data Analysis |
| | Provide a description of your plan for data analysis. State the types of comparisons you plan (e.g. comparison of means, comparison of proportions, regressions, analysis of variance). Which is the PRIMARY comparison/analysis? How will the analyses proposed relate to the primary purposes of your study? | | --- | | |  | Descriptive statistics will be used to summarize basic demographic information and drug use variables. Placebo vs. medication groups will be compared using one–way ANOVA. If significant differences between treatment groups are identified, then these variables can be included in further analyses as covariates. General linear models for repeated measures will be used to assess placebo vs. medication effects on cardiovascular responses, subjective effects, or reinforcing effects. | | --- | --- | | |
|  |
| **Section H:  Potential Risks/Discomforts** |
| H1.  Potential Risks/Discomforts |

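### The 0.80 power needs 20 people with both phases, but the protocol makes the second phase optional and does not define a completer; the total of 200 covers only one of two possible groups

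*Protocol*

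**What the plan says.** Protocol F1 (Design) sets out a crossover: "Twenty participants will complete procedures during treatment with placebo and study medication, in random order, using a within-subjects, double-blind, placebo-controlled design". G1 (Sample Size) gives the matching calculation: "For a sample size of 20, with an alpha level of 0.05, a paired t-test indicates power of approximately 0.80". The planning effect is a halving of the Feel High rating ("We anticipate a reduction by one-half as a clinically significant treatment effect"). Its variability is left to a cited report on intravenous cocaine, and no mean or standard deviation is stated.

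F2 (Procedure) differs. Participants will be asked to go through the protocol twice, "once being randomized to placebo and once being randomized to doxazosin, but this wont be required". Its discharge paragraph repeats the point: "Participants will have the choice of returning two weeks later to complete study procedures".

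On numbers, G1 says "To have twenty completers, we may need to enroll up to 30 participants and thus screen/consent 200 potential subjects" and enters 200 as both the local and the worldwide total. F1 adds that if 4 mg is well tolerated but does not alter the effects of cocaine, "a second group of subjects will be studied using the same sample size".

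The payment plan in Section L describes the larger Day 11 payment, which falls within a single phase, as a bonus for completing the study. It then sets a separate bonus for people who complete both phases.

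**The concern.** A paired t-test uses only people measured under both conditions. F1 and G1 count 20 such people, while F2 does not require anyone to become one. This goes beyond the ordinary right to withdraw, because the planned procedure itself makes the second phase elective. The word completer does not settle the matter: G1 leaves it undefined, and Section L applies completion to one phase as well as to two. Staff working from F2 and Section L could count someone as complete who contributes no pair.

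Two things are at stake.

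- **Power.** It falls with each missing pair below 20. This may also affect the second group, which opens when 4 mg appears not to alter the effects of cocaine. If that judgement rests on the powered comparison, which the protocol does not say, a missed effect at 4 mg would open a further group.
- **Selection.** Return is chosen after the first phase has been experienced, so it may depend on how the study drug was tolerated or how cocaine felt.

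A separate and smaller matter is that the total of 200 follows from the need for one set of twenty completers, although the design allows two.

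**Working it through.** **Inputs from the documents.** n = 20, alpha 0.05, paired t-test, power about 0.80, 50% reduction in Feel High, up to 30 enrolled and 200 screened or consented for twenty completers (all G1); a possible second group of the same size (F1).

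**Not in the documents.** The sidedness of the test, the placebo mean, and the standard deviation (SD) of the paired differences. Both one-sided and two-sided results are therefore shown.

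**Step 1: the plan's own figure.** Without an SD, 0.80 cannot be computed forwards. It can be solved backwards for the standardised paired effect dz (mean difference divided by SD of differences). For n pairs, two-sided power is P(|T| > t(0.975, n−1)), where T is noncentral t with n−1 degrees of freedom and noncentrality dz × √n. The one-sided version uses P(T > t(0.95, n−1)).

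- Two-sided, n = 20: critical value 2.093. Power 0.80 needs noncentrality 2.954, so dz = 2.954/√20 = 0.660.
- One-sided, n = 20: critical value 1.729. Power 0.80 needs noncentrality 2.580, so dz = 2.580/√20 = 0.577.

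For a 50% reduction, the two-sided value implies an SD of differences of 0.5/0.660 = 0.76 of the placebo mean. Two-sided power at 20 pairs would be 0.94 if that ratio were 0.60 and 0.56 if it were 1.00. So 0.80 is plausible at 20 pairs, but the document alone can neither confirm nor refute it.

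**Step 2: power by number of pairs, with the implied dz held fixed.**

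| Pairs | Share of 30 enrolled | Two-sided (dz 0.660) | One-sided (dz 0.577) |
|---|---|---|---|
| 20 | 67% | 0.80 | 0.80 |
| 18 | 60% | 0.75 | 0.76 |
| 15 | 50% | 0.66 | 0.68 |
| 12 | 40% | 0.55 | 0.59 |
| 10 | 33% | 0.46 | 0.52 |

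The chance of missing the planning effect is thus 20% at 20 pairs and 48% to 54% at 10.

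**Step 3: what the enrolment allowance covers.** 20/30 = 0.67, so G1 allows for one third lost: 20/(1 − 1/3) = 30. If at least two thirds of 30 finish both phases, 0.80 is kept. The text does not say whether this third is meant to include people who finish one phase and choose not to return.

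**Step 4: totals.** G1's chain is 20 completers, up to 30 enrolled, 200 consented. A second group of equal size doubles each: 2 × 20 = 40, 2 × 30 = 60, 2 × 200 = 400. The stated total is 200. If 200 had to serve both groups at the same ratios, each would yield about 10 completers, which is the last row of the table if those completers are pairs.

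**The case against.** The best defence is that the protocol, read as a whole, intends both phases. F1 says so directly. In G1, the twenty completers follow immediately after a paired test on 20. F2 speaks of returning in order to complete procedures, and the stated duration of about 28 days suits two stays rather than one. Section L rewards return, with $1400 plus a $100 bonus for both phases against $660 listed for one. G1 already allows for a one-third loss. No return rate is given, so the rows below 20 pairs are illustrations and not forecasts. Any crossover can lose people between periods, and the handling of one-period participants commonly belongs in the analysis plan, which is not shown. The repeated-measures models in G2 might also use one-phase data, depending on how they are fitted.

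Much of this stands, and it limits the point. A reader might infer any of the following, and the documents support none of them:

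- **That 0.80 is wrong.** It is not shown to be wrong at 20 pairs; the SD needed to test it is not given.
- **That 20 people with one phase each would satisfy the plan, leaving an unpaired comparison of 10 with 10.** That would contradict F1, and its power depends on a within-person correlation that the documents do not give.
- **That the results will be biased.** Selective return is possible, but nothing in the documents shows or excludes it.
- **That the approved total is certain to run out.** The 200 is a screening and consent count, the 30 is worded as an upper limit, and the second group is conditional.

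The defence does not remove the conflict itself. Evidence of intent in F1 and G1 does not cancel two statements in F2 that the second phase is elective. An analysis plan cannot create pairs that the procedure did not require.

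**Conclusion.** The point holds in a limited form, as something that should be fixed. F2 contradicts F1 and G1 on whether both phases are part of the design, and completer is not tied to both day-10 sessions. The stated power is conditional on 20 pairs, that is, on at least two thirds of the 30 enrolled finishing both phases. Short of that, it drops to about two thirds at 15 pairs and about one half at 10. These figures assume that the plan's 0.80 at 20 pairs is correct and that the same effect size applies to whoever returns; the ranges cover unstated sidedness only.

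The total is a minor part. The 200 makes no provision for the second group, and the doubled figures arise only if that group opens.

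**What to change.** 1. Reconcile F2 with F1 and G1: plan and consent participants for both phases, keeping the usual right to withdraw, and remove the wording that makes the second phase elective.
2. In G1, define a completer as a participant with both day-10 sessions, and use the word the same way in Section L.
3. Recruit to 20 such completers within the up to 30 planned. If fewer than two thirds finish both phases, 30 will not yield 20 pairs; in that case restate power for the number of pairs obtained.
4. State in G1 the SD of paired differences and the sidedness behind the 0.80, so that it can be checked.
5. Give the totals both ways: 200 consented and up to 30 enrolled for one group, 400 and up to 60 if the second group opens.

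The cost is protocol and consent wording, and a lower stated power if 20 pairs are not reached. No participants are added beyond those the plan already implies.
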